### Adaptation of the iCBT programme for breast cancer survivors

1.2

Space from Depression and Anxiety is an 8-week CBT based online intervention programme, designed originally for the treatment of depression and anxiety symptoms in the general population and adapted for the breast cancer context for this study. The original Space from Depression programme (without the anxiety module) has been found effective for adults with depressive symptoms in the general population, with a large effect size at post-treatment (d = 0.91; Richards et al., 2015). The differences between treatment and waiting-list control group also yielded statistically significant results, with a moderate to large effect size (d = 0.50), and these improvements on the outcomes were maintained at 6-month follow-up. Most participants reported that they were satisfied with the programme, felt supported, reported positive gains and impact, and perceived these as lasting effects (Richards et al., 2016). However, the programme content (e.g., examples and personal stories) was not suitable for the breast cancer survivor and carer context, thus adaptation was required. In a recent randomised waitlist-controlled effectiveness and cost-effectiveness trial of digital interventions, it was found that 8-week iCBT for depression and anxiety is not only effective but also potentially cost-effective in the long-term within the improving access to psychological therapies programme (IAPT) in the UK (Richards et al., 2020).

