### Sample size

2.4

The G-Power software programme was used to carry out power analysis and determine the sample size needed for three-group, pre-test, post-test, and follow-up design. The data from a randomised controlled trial of an iCBT programme for depression and anxiety among cancer survivors revealed a large within-between interaction effect size for the HADS-Total after comparing the pre-treatment and post-treatment scores of the iCBT and the TAU (Murphy et al., 2019). To calculate the sample size, we powered for the changes in the primary outcome (depression and anxiety symptoms, measured by the HADS-Total) when comparing the treatment groups (iCBT alone and iCBT with the carer access) with the TAU. Assuming a medium effect size (*f* = 0.30) for the pre, post, follow-up comparisons between iCBT alone, iCBT with carer access, and TAU with a power of 0.80 and significance level of α = 0.05, the sample size is calculated to be 27 breast cancer survivors in each group and 81 in total (54 in the iCBT group and 27 in the TAU group using 2:1 ratio). Considering the 25% attrition (Richards et al., 2018), 108 breast cancer survivors in total (*n* = 72 for iCBT and = 36 for TAU) will be recruited.

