Secondly, no study to date has examined the effectiveness of including informal carers in the survivors' intervention programme targeting their depression and anxiety symptoms. This pilot trial is novel as it further aims to explore whether giving main carers (i.e., partners, family members, friends) access to survivors' iCBT treatment makes a difference on survivors' anxiety and depression symptoms, social support perceptions, and cancer-related communication quality, and relationship quality with their carers as well as carers' cancer-related communication quality, and relationship quality with survivors. This study will provide novel insight regarding the feasibility of carer access based on the number of survivors who prefers to give their carers access to the iCBT programme. The trial is sufficiently powered for testing the primary and secondary hypotheses, and analyses regarding the effects of the iCBT with the carer access are more exploratory. As the iCBT alone and iCBT with the carer access group assignment is based on survivors' preference due to its exploratory nature, the study may be underpowered for detecting those effects in the exploratory analyses. Therefore, the results of the exploratory analyses will be interpreted with caution.

Another notable strength of this study is that it uses a mixed-methods approach by combining quantitative methods to measure the programme effectiveness with qualitative measures through HAT and SAT to assess the user experiences and satisfaction, which will provide rich information and help us to better understand the nature of the existing relationship between outcomes. If the programme is found feasible and a clinically significant difference is found in depression and anxiety symptoms of survivors, the iCBT programme may be used as an alternative within stepped care of breast cancer patients and survivors, where guided low-intensity interventions are an attractive option (Richards et al., 2018).

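### The 81 analysable women do not follow from the stated inputs at default G*Power settings (27 in total), and the calculation does not establish 80% power for a moderate iCBT-TAU effect

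*Protocol article*

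**What the plan says.** Section 2.4 of the protocol article (Sample size) reports that "The G-Power software programme was used to carry out power analysis" and "determine the sample size needed for three-group, pre-test, post-test, and follow-up design". It cites an earlier iCBT trial in cancer survivors that "revealed a large within-between interaction effect size for the HADS-Total", and says that "we powered for the changes in the primary outcome", HADS-Total, for the two iCBT groups against TAU. The assumption is "Assuming a medium effect size (*f* = 0.30", with power 0.80 and alpha 0.05. The result is that "the sample size is calculated to be 27 breast cancer survivors in each group and 81 in total", split 54 to 27, then raised to 108 (72 and 36) for 25% attrition. The correlation among repeated measures, the nonsphericity value and the effect-size option are not given.

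Three other places bear on this:

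- Section 2.10.2 takes 0.20, 0.50 and 0.80 as small, moderate and large standardised differences.
- Section 1.2 reports a between-group result for the original depression programme "with a moderate to large effect size (d = 0.50" against a waiting list.
- The Discussion concludes: "The trial is sufficiently powered for testing the primary and secondary hypotheses". It concedes possible low power only for the exploratory carer-access comparisons.

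**The concern.** The wording points to one test: the repeated-measures within-between interaction with three groups and three measurements. At default settings that test returns 27 as the total, which is the number the article reports per group.

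The matter goes beyond a labelling slip, because the effect size is also mislabelled on that scale. An f of 0.30 that can be detected with 27 women in all cannot be a medium treatment effect. The 80% in section 2.4 therefore does not tell a reader what the trial can detect. The Discussion nevertheless builds a general statement of sufficient power on it, covering H2 to H5 and so the two mediation hypotheses. A null result would be read against a power figure that the calculation does not support.

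**Working it through.** **Inputs from the article.** k = 3 groups, m = 3 time points, f = 0.30, power 0.80, alpha 0.05, 54 versus 27 analysable, 25% attrition (all section 2.4); moderate d = 0.50 (section 2.10.2). **Assumed, because not stated:** correlation rho = 0.5 and epsilon = 1 (G*Power defaults), both varied below.

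**1. The plan's own figure.** Within-between interaction, default effect-size option:

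lambda = f² · N · m · epsilon / (1 − rho), df1 = (k − 1)(m − 1) · epsilon, df2 = (N − k)(m − 1) · epsilon.

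At N = 27, lambda = 0.09 × 27 × 3 / 0.5 = 14.58, with df 4 and 48.

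| N in total | Power |
|---|---|
| 24 | 0.786 |
| 25 | 0.807 |
| 27 | 0.844 |
| 81 | above 0.999 |

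The smallest N with equal groups is 27 in total, or 9 per group. Changing rho does not lead to 81: the total is 48 at rho 0, 36 at 0.3 and 18 at 0.7.

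**2. Settings that do give 81 (equal groups).**

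| Test | Setting | Total N |
|---|---|---|
| Interaction, 'as in SPSS': lambda = f²(N − k)(m − 1)·epsilon | epsilon 1 | 72 |
| | epsilon 0.85 | 81 |
| Interaction, 'as in Cohen': lambda = f²·N(m − 1)·epsilon | epsilon 1 | 69 |
| | epsilon 0.80 | 81 |
| Between factors: lambda = f²·N·m / (1 + (m − 1)·rho) | rho 0.5 | 75 |
| | rho about 0.55 to 0.59 | 81 |

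Each route to 81 needs a non-default value that the article does not state.

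**3. Attrition.** 81 / 0.75 = 108, 54 / 0.75 = 72 and 27 / 0.75 = 36. This step is correct.

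**4. What f = 0.30 means on the default scale.** Take a gap of 0 at baseline and d SD at both later times, with two thirds of the women on iCBT. The variance of the time pattern (0, d, d) is (2/9)d², and the allocation factor is (2/3)(1/3) = 2/9. Hence f = √[(2/9)(2/9)] · d = (2/9)d, and d = 0.30 × 9/2 = 1.35. Conversely, d = 0.50 corresponds to f = 0.11.

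**5. Power of 54 versus 27 for d = 0.50.** Two-sided noncentral t with 79 df and noncentrality d* · √(54 × 27 / 81) = d* × 4.243. Here d* = d / √[2(1 − r)] for a change score, and d* = d / √(1 − r²) with baseline adjustment.

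| r | Change score | Baseline-adjusted | Detectable d at 80%, baseline-adjusted |
|---|---|---|---|
| 0.4 | 48% | 63% | 0.61 |
| 0.5 | 55% | 68% | 0.58 |
| 0.6 | 65% | 75% | 0.53 |
| 0.7 | 77% | 84% | 0.48 |

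At one time point, 80% needs r of at least about 0.66 with baseline adjustment, or about 0.72 for a change score. If post-treatment and follow-up are averaged at r = 0.5, the variance factor with baseline adjustment is (1 + r)/2 − r² = 0.50, and power is 84%. The averaged change score gives 68%. The 3×3 interaction test with 81 women gives 46% at rho 0.5 and 70% at rho 0.7.

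**The case against.** The strongest reply is that the article condenses a fuller calculation. The interaction test itself returns 81 under either alternative effect-size option with mild nonsphericity, and 72 or 69 without it. That stands: the mismatch is shown only at default settings, and the total-for-per-group slip is an inference from the matching number. The 1.35 SD is tied to the same default; under 'as in Cohen' at rho 0.5, f = 0.30 corresponds to about 0.78 SD, which is close to the article's own mark for large.

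A reader might infer that the trial is underpowered outright. The documents do not support that:

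- The shortfall appears when d = 0.50 replaces the article's f = 0.30. If f = 0.30 is read as a group difference at one time point, d = 0.30 / √(2/9) = 0.64, and power is 76% unadjusted but 87% with baseline adjustment at r = 0.5.
- Even at d = 0.50, a high enough correlation, or averaging the two later assessments with baseline adjustment, reaches 80%.
- If the slip occurred, it tripled the sample relative to the stated calculation.

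A reader might also infer that the trial cannot detect the effect already seen for this programme. The d = 0.50 in section 1.2 belongs to the original depression programme, without the anxiety module, in general-population adults against a waiting list. It is not an estimate for the adapted programme against TAU.

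Finally, section 2.4 does give 54 versus 27 for the randomised comparison, and the Discussion admits the uncertainty from the preference split. Neither supplies a power figure for pooled iCBT versus TAU, or any calculation for the secondary hypotheses.

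**Conclusion.** The point holds in a limited form. Under default settings the stated inputs lead to 27 women in total rather than 81, and the article names no setting that would lead to 81. On that default scale the effect is about 1.35 SD and is not medium by the article's own benchmark.

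For d = 0.50 with 54 versus 27 analysable, power runs from about 55% (one time point, change score, r = 0.5) to about 84% (baseline-adjusted at r = 0.7, or both later time points averaged with baseline adjustment at r = 0.5). The conclusion is that 80% power for a moderate effect has not been established; it is not that such power is absent. These figures assume equal variances, 25% loss as planned and the correlations shown.

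The claim of sufficient power for the secondary hypotheses is unsupported whichever setting was used, since the only calculation concerns HADS-Total.

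**What to change.** Keep N = 108 and change the text in three places.

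1. **Section 2.4, calculation.** State which G*Power test was run, with its correlation, epsilon and effect-size option. Restate power for the randomised contrast, for example: with 54 iCBT and 27 TAU women analysable and a two-sided 5% level, the trial has 80% power for d of about 0.58 on HADS-Total at post-treatment, baseline-adjusted, assuming r = 0.5 (0.61 at r = 0.4, 0.53 at r = 0.6); power for d = 0.50 is about 68% (63% to 84% for r = 0.4 to 0.7).
2. **Section 2.4, group sizes.** Stop presenting 27 per group as a powered quantity. The two iCBT groups form by preference, so their sizes are not fixed by design.
3. **Discussion.** Limit the statement of sufficient power to the primary contrast as restated, and say that H2 to H5 are not separately powered.

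The cost is wording and a less favourable power statement. No extra participants are needed, and the design and analysis do not change.

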### Randomisation

2.5

Eligible participants will be randomly assigned to either iCBT intervention (n = 72) or treatment-as-usual control (*n* = 36) with a 2:1 ratio. Those who are assigned to iCBT group and have carers will be asked whether they will participate with or without their main carer. Participants will be assigned to iCBT alone or iCBT with carer access based on their preference and informed immediately about their group assignment. Survivors in the iCBT alone group (Group 1) will be using the iCBT programme by themselves, and survivors in the iCBT with the main carer access group (Group 2) will be using the same programme, but their main carers will also have access to the programme content using a separate username and password. Participants in the treatment-as-usual control group (Group 3) will continue their usual care and will not receive the iCBT programme during this study. They will fill out the same measures as the other two groups at pre-treatment, post-treatment, and 2-month follow-up.

### Procedure

2.6

The link on the advertisement will direct potential participants to a Qualtrics page to complete the informed consent, screening questionnaire assessing inclusion criteria, demographic information, and health status. All participants will be responsible for self-screening as their eligibility will be determined based on their responses to the questions set-up in Qualtrics. The survey is designed to automatically exclude respondents who select “yes” to the questions asking current suicidal ideation or intent, current alcohol or drug misuse, and organic mental health condition (such as schizophrenia, psychosis, and bipolar disorder), and current psychotherapy for depression or anxiety. Potential participants who responded yes to the questions regarding current suicidal ideation and intent will see a message providing contact details for recommended support services on the screen. Eligible survivors will be able to continue with baseline questionnaires (Time 1) assessing depression and anxiety symptoms, quality of life, fear of recurrence, coping, perceived social support, relationship quality, and cancer-related communication. After filling out the questionnaires, eligible participants will be automatically randomised and those who prefer to participate with their carer (iCBT with the main carer access) will be asked to provide their carers' email address on the Qualtrics page. Carers will be contacted through the email address provided by breast cancer survivors and asked to complete the informed consent, screening questionnaire, and survivor-carer cancer communication, and relationship quality measures through a separate Qualtrics link. All survivors and carers will be reassessed online at the end of the intervention (7 weeks after they started, Time 2), and at 2-month follow-up (Time 3). At the end of the intervention, survivors and their main carers in both treatment groups will be asked about their perspectives on the helpful aspects of the programme and their satisfaction with the programme.

### iCBT intervention: space in breast cancer from depression and anxiety

2.7

*Space in Breast Cancer from Depression and Anxiety* is a seven module CBT-based intervention for depression and anxiety adapted specifically for women breast cancer survivors and their informal main carers. The programme was designed to alleviate depression and anxiety symptoms through the use of CBT skills such as activity planning (behavioural activation), understanding the role of feelings, identification of unhelpful or irrational thinking patterns, generating more realistic and helpful thoughts by changing their perspective (cognitive restructuring), setting up a worry time, and differentiating practical and hypothetical worries.

It consists of 7 modules completed ideally over 7 weeks and each takes approximately an hour to complete. A brief description of the programme content in each module can be seen in Table 1. There are also additional resources and tools available in the programme such as a journal, mindfulness and relaxation audio exercises, activity scheduling, activities list, and mood monitor. Each module in the programme includes quizzes, personal stories, exercises, and a summary.

**Table 1 t0005:** Content of the intervention programme.

Module	Description
1. Getting started	This module provides information about breast cancer, depression, and anxiety, and why do they occur in breast cancer survivors. It also introduces the basics of CBT.
2. Understanding feelings	This module introduces emotions, outlines the function of them, and how they are related to our physical body reactions. It also encourages users to express their emotions and includes examples about how to do it tactfully.
3. Boosting behaviour	Boosting behaviour is a module focusing on behavioural activation as a way to improve users' mood. It helps them to identify and plan pleasurable activities that will give them a sense of achievement and help them feel better.
4. Spotting thoughts	This module aims to help users identify their unhelpful, negative thinking patterns, distorted thinking errors, and builds their own TFB cycles.
5. Challenging thoughts	Challenging Thoughts module helps users to identify and challenge their unhelpful hot thoughts and find an alternative thought that is more balanced and realistic.
6. Managing worry	This module explains the role of worry in anxiety and introduces the worry cycle. It also introduces techniques to manage both real and hypothetical worries.
7. Bringing it all together	This module encourages users to reflect on what information and skills they have learned and helps them to make a plan to stay well by watching out for personal warning signs and maintaining social support.

### Supporters

2.8

As this is a guided iCBT intervention, each survivor will be assigned a supporter, who provides weekly feedback on their progress on the programme. The supporters are masters' level students in applied psychology who have completed an undergraduate degree in Psychology. They were given an online health supporter training by an experienced psychologist from SilverCloud Health. The training took 1.5 h and the aim was to make supporters to become familiar with the evidence base of iCBT, to provide them a working knowledge of the platform being used, and help them communicate effectively with the users through demonstrating how to write reviews. The supporters were also given psycho-education training on breast cancer and its psychological impacts by the principal researcher [name] before starting their role as a supporter. Supporters will be provided weekly supervision by the researchers [name].

Each supporter will provide asynchronous weekly feedback on the platform to their assigned users. Feedback will take 10 to 15 min per participant for each session, which will consist of motivating users to keep using the programme, providing feedback on their progress, and suggesting the use of specific helpful tools in the programme. Supporters will schedule a specific time for feedback each week for a period of seven weeks so that survivors will know when they will get the feedback.

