#### Effectiveness analyses for primary and secondary outcomes

2.10.2

Linear Mixed Modelling (LMM) will be used to compare pre-treatment, post-treatment, and 2-month follow-up scores of the survivors in three groups (iCBT alone, iCBT with the carer, and TAU control) on the main outcome measure of depression and anxiety as well as secondary outcome measures including cancer-related quality of life, coping, and fear of cancer recurrence. The intention-to-treat (ITT) and per-protocol (PP) approach will be used to test the effectiveness of the treatment groups over the TAU control group. According to the ITT approach, participants who leave the study early or do not comply with the protocol are considered as belonging to the treatment arm they were originally randomised to. On the other hand, PP analytical approach does not include patients who violate the protocol, switch the allocation arm throughout the study, do not adhere to the assigned treatment or do not undergo to the scheduled assessments over time. Thus, it helps capture the “true” exposure to treatment. As suggested, the ITT will be used as the main method of analysis to determine effectiveness as it provides an unbiased estimate to treatment effect, and the PP will be used as a secondary and supportive analysis (Tripepi et al., 2020) to provide complementary information about the iCBT intervention. Restricted maximum likelihood (REML) estimation will be used to account for missing data due to participant drop-out. Significant effects will be followed up using pairwise contrasts comparing mean pre-treatment scores to post-treatment scores. Between-group (Hedges' *g*) and within-group (Cohen's *d*) effect sizes will be calculated using the pooled standard deviation and adjusted for sample size. For Hedges' *g* and Cohen's *d* an effect size 0.20 is considered small, 0.50 moderate, and 0.80 large.

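### iCBT women are nested within supporters and TAU women are not, but the stated model and sample size make no allowance for it; if supporters differ, the iCBT–TAU standard error is too small

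*Protocol article*

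**What the plan says.** The Supporters section (2.8) describes a guided intervention in which "each survivor will be assigned a supporter, who provides weekly feedback on their progress on the programme". The same section implies a caseload for each supporter: "Each supporter will provide asynchronous weekly feedback on the platform to their assigned users". It says who gives the guidance: "The supporters are masters' level students in applied psychology who have completed an undergraduate degree in Psychology". It also describes common training, "Supporters will be provided weekly supervision by the researchers", and limited contact: "Feedback will take 10 to 15 min per participant for each session". It does not give the number of supporters, the caseload or the way supporters are matched to women.

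Under Randomisation (2.5), TAU women "will continue their usual care and will not receive the iCBT programme during this study", so they have no supporter. Within the iCBT arm, "Participants will be assigned to iCBT alone or iCBT with carer access based on their preference".

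The effectiveness analysis (2.10.2) states that "Linear Mixed Modelling (LMM) will be used to compare pre-treatment, post-treatment, and 2-month follow-up scores of the survivors in three groups". It names REML as the estimator. It does not describe the random effects and mentions no term for supporter. The Sample size section (2.4) reaches 81 evaluable women (54 iCBT, 27 TAU) and 108 recruited, with attrition as the only inflation. The Discussion says the trial has enough power for its primary and secondary hypotheses.

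**The concern.** Women who share a supporter share that person's skill, tone and diligence over seven weeks of feedback, so their post-treatment scores may be correlated. TAU scores carry no such correlation. A model without supporter counts the iCBT women as more independent information than they supply. The standard error of the iCBT–TAU difference is then too small, its interval too narrow and its type I error above the nominal level. The stated power also has no margin for the loss.

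A second effect is possible in the carer-access comparison. If some supporters mainly serve Group 1 and others mainly Group 2, differences between supporters are mixed with the effect of carer access. Supporter identity has to be captured during conduct, because no later analysis can adjust for a supporter who was never recorded.

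**Working it through.** **The plan's own figures.** The attrition step reproduces exactly: 81/0.75 = 108, 54/0.75 = 72 and 27/0.75 = 36. The 81 cannot be checked uniquely, because the test and the correlation between repeated measures are not stated. A between-groups repeated-measures F test with f = 0.30 and a correlation of about 0.59 gives power 0.80 at 81. Neither step contains a design effect.

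**Inputs.** From the article: 54 v 27 evaluable women, 2:1 allocation, α = 0.05, supporters in the iCBT arm only. Assumed, because the article does not give them: number of supporters J = 4 to 12 and supporter ICC ρ = 0.01 to 0.10.

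**Formulas.** Women per supporter: m = 54/J. Design effect, iCBT arm only: DE = 1 + (m − 1)ρ. Ratio of correct to naive standard error: R = √[(DE/54 + 1/27)/(1/54 + 1/27)]. True two-sided error: 2[1 − Φ(1.96/R)].

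**Example, J = 6 and ρ = 0.05.** m = 9 and DE = 1 + 8 × 0.05 = 1.40. R = √[(0.02593 + 0.03704)/(0.01852 + 0.03704)] = √(0.06296/0.05556) = 1.065. Error = 2[1 − Φ(1.841)] = 0.066.

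| J | ρ = 0.01 | ρ = 0.02 | ρ = 0.05 | ρ = 0.10 |
|---|---|---|---|---|
| 4 | R 1.02, error 0.055 | 1.04, 0.060 | 1.10, 0.075 | 1.19, 0.100 |
| 6 | 1.01, 0.053 | 1.03, 0.056 | 1.06, 0.066 | 1.13, 0.082 |
| 8 | 1.01, 0.052 | 1.02, 0.054 | 1.05, 0.061 | 1.09, 0.073 |
| 12 | 1.01, 0.051 | 1.01, 0.053 | 1.03, 0.057 | 1.06, 0.064 |

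Simulation (40,000 runs per cell) agrees closely, for example 0.074 at J = 4, ρ = 0.05 and 0.104 at J = 4, ρ = 0.10. The formula is for a comparison of two means at one time. It carries over to change from baseline if ρ is read as the ICC of the change.

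**Power.** Take the difference that gives 80% power at 54 v 27 without clustering. With the correct standard error, power is between 0.795 (J = 12, ρ = 0.01) and 0.653 (J = 4, ρ = 0.10).

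**Group 1 v Group 2.** By simulation over J = 4 to 12 and the same ICCs, the error stays at 0.038 to 0.050 if every supporter serves both groups evenly. It is 0.054 to 0.194 if supporters are split by group.

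**Which supporter term works.** Baseline is completed before randomisation (Procedure, 2.6), so a supporter can affect only later scores. If the model adds the same supporter intercept u to every visit, the change is (Y₁ + u) − (Y₀ + u) = Y₁ − Y₀, and u cancels. With the variance of the change set to 1, the standard error is √(1/54 + 1/27) = 0.2357 with or without that intercept (complete data). If the effect acts after baseline with variance 0.05 over six supporters, it is √(1/54 + 1/27 + 0.05/6) = 0.2528, about 7% larger.

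**Zero variance estimates.** With six supporters of nine women and a true ICC of 0.05 in a single-time analysis, the ratio of expected mean squares is 1 + 9 × 0.05/0.95 = 1.474. The variance is estimated as zero or below when F on 5 and 48 df is under 1/1.474 = 0.679, which has probability 0.36.

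**The case against.** The strongest reply is that much of this rests on silence. A condensed article commonly leaves the random-effects structure to a fuller document. A reader might infer that the plan treats all women as independent, or that the pool of supporters is small. The article says neither: it does not describe the random effects at all and gives no count of supporters. Both readings should be set aside.

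The ICC may also be close to zero. The treatment is a fixed seven-module programme. Supporters share the same training and weekly supervision, and contact is brief and asynchronous. At 12 supporters and an ICC of 0.01 the error is 0.051, which is of no consequence.

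A reader might also infer that the carer-access comparison is confounded by supporter. That needs an uneven spread of supporters over the two groups, which the article does not report. The comparison is in any case by preference, labelled exploratory, and already flagged as possibly underpowered and to be interpreted cautiously. Self-selection is the larger threat there, and it is disclosed.

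These replies limit the claim but do not remove it. The nesting is stated in the article. The sample-size calculation is given with its inflation step, and clustering is not in it. The cautions about the exploratory comparison concern preference and power, not supporter imbalance, which a rotation can prevent.

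**Conclusion.** The point holds in a limited form. The design is partially nested by supporter, and neither the model as described nor the sample size allows for it. With any positive supporter ICC, a model without supporter understates the iCBT–TAU standard error. The direction is certain under that condition, but the size cannot be fixed from the article. On the assumed ranges (4 to 12 supporters, ICC 0.01 to 0.10, 54 v 27 women) the correct standard error is about 1.01 to 1.19 times the naive one, and the true two-sided error is 0.051 to 0.100.

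The documents do not support the conclusion that the trial's intervals will certainly be too narrow, since the ICC could be zero. This is a cheap improvement to a pilot trial, not a fault that invalidates it.

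**What to change.** 1. Record supporter ID for every iCBT woman, including those already enrolled (recruitment opened on 30 October 2020).
2. For women still to be enrolled, assign supporters by random rotation, run separately within Group 1 and Group 2, so that each supporter serves both groups.
3. Pre-specify, at least as a sensitivity analysis, a mixed model with a supporter random effect for the iCBT arm only that acts at the post-baseline visits (supporter-by-time, set to zero at baseline and for TAU), with small-sample degrees of freedom. A time-constant supporter intercept does not do this job.
4. Do not read a zero variance estimate as proof of no clustering. Report the iCBT–TAU result over a stated range of assumed ICCs.
5. State the number of supporters and the caseload of each.

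The cost is one recorded variable, a rotation list and one extra model term. With few supporters the variance will be imprecise, and intervals may be slightly wider.
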